### Study endpoints

#### Primary endpoint

The primary endpoint is change in International Knee Documentation Committee (IKDC) from baseline (pre-rupture) to 6 months post-operatively. The difference in IKDC score between the reconstruction technique and the repair techniques (DIS/IBLA) is expected to be the largest at 6 months postoperatively, due to the proprioceptive conservation with the repair techniques.

The IKDC is a commonly used instrument to determine the outcome following various knee procedures, including ACL reconstructions [28]. In essence, it is a subjective well-known tool that provides patients with an overall function score (range 0–100). The score is interpreted as a measure of function with higher scores representing higher levels of function. The questionnaire addresses three categories: symptoms (pain, swelling, stiffness, etc.), activity (rising from chair, going up and down stairs, jumping, squatting, etc.) and knee function [29].

#### Secondary endpoints

Pain experienced by the patients as measured by Visual Analogue Scale (VAS) pain score [30, 31].Overall functioning by the patient, related to the knee, as measured by Tegner and Lysholm score [32].Health-Related Quality of Life (HRQoL) as measured by EQ-5D-5 L [33, 34].Time to recovery as measured by mobilization with crutches, return to work and sports.Patient satisfaction towards the surgery and revalidation level as measured by VAS satisfaction.Mechanic functioning of the knee as measured by Lachman test; single leg hop, triple leg hop, triple crossover hop and drop jump test; proprioceptive measurement; isokinetic measurement; and knee function [35–42].Intra- and post-operative complications: adverse device effects (ADEs) and serious adverse events (SAEs).Success of the operation techniques defined as the number of non-failures.
A failure is defined as:
A re-rupture of the graft or the repaired ACL: clinically and MRI-confirmedInstability complaints: AP translation difference of more than 3 mm (Lachman test) between the injured knee and the contralateral knee, and subjective instability complaints [17].The number of physiotherapy and (extra) orthopaedic surgeon consults.ACL healing will be evaluated with MRI [43].

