Since the mid-eighties the gold standard for an operative treatment of an ACL rupture is reconstruction with a tendon graft. This involves removing native ACL tissue including its proprioceptors. The ligament is often replaced with autograft donor tendon(s), such as a hamstrings tendon or a part of the patellar tendon. A number of problems have been identified as graft harvest is associated with a degree of morbidity from tissue loss. Hamstrings muscle weakness following harvesting averages 10% in most studies [7]. Revascularization of the graft takes 6–12 months and ingrowth of the graft in the bone takes up to 2 years [8]. Another disadvantage of conventional ACL reconstruction is the rather long period of revalidation associated with a huge socio-economic burden. A successful recovery from an ACL reconstruction encompasses intensive physiotherapy and requires a lot of effort, dedication, time and perseverance. According to Ardern et al. [9], the return to competitive sports after ACL reconstruction is only 44 to 55%. In another study, Biau et al. [10] found that only 40% of patients gain full functional recovery. Nagelli and Hewett postulated that delay in returning to sports for the first 2 years will significantly reduce the incidence of second ACL injuries [11]. Given the limitations and risks associated with the current gold standard treatment of an ACL rupture, there is room for improvement.

The last few years there is a renewed interest in ACL repair as an alternative operative treatment for the acute ruptured ACL. Two novel surgical ACL repair techniques have been developed and proof of concept has been established for treating an acute ACL rupture: Dynamic Intraligamentary Stabilization (DIS, Ligamys®, Mathys Ltd., Bettlach, Switzerland) and Internal Brace Ligament Augmentation (IBLA, *Internal*Brace™, Arthrex GmbH, Naples, Florida) repair techniques [12, 13].

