#### Secondary objectives

To assess whether DIS and IBLA offer an improvement in quality of life, patient satisfaction and functioning of the patient compared to conventional ACL reconstruction.To assess whether DIS and IBLA result in a shorter recovery period compared to conventional ACL reconstruction in terms of the mobilization period with crutches after the surgery, and return to work and sports period.To assess whether there is a difference between DIS and IBLA versus conventional ACL reconstruction in terms of pain and complications during and after surgery.To assess whether there is a difference between DIS and IBLA versus conventional ACL reconstruction in terms of ACL re-ruptures/failures.To determine the economic benefit of the two alternative techniques DIS and IBLA in comparison to the conventional ACL reconstruction for treating an acute ACL rupture.For all of these objectives also the mutual comparison between DIS and IBLA will be considered.

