**Fig. 1 Fig1:**
[figure not shown]
Study flow diagram: screening, inclusion, surgery and follow-up. *Depends on when the patient presents at the consultation desk after the ACL rupture. **Patients in the exploratory group will be replaced, but are still part of the study. ACL = Anterior Cruciate Ligament, DIS = Dynamic Intraligamentary Stabilization, IBLA = Internal Brace Ligament Augmentation, MRI = Magnetic Resonance Imaging

Allocation to either study 1 or study 2 depends on the patient’s admission time point after ACL injury and if it is practically feasible to perform ACL surgery within 4 weeks. There is a patient and referral delay, a magnetic resonance imaging (MRI) needs to be performed to confirm the ACL rupture and the surgery has to be planned. On the other hand, inclusion and surgery between week 5–12 after injury is expected to be more manageable to plan. There will be an intra-operative confirmation in study 1 and study 2 of the ACL’s eligibility for repair. If the proximal ACL rupture is not suitable for repair, ACL reconstruction will be performed. To keep the three arms (DIS, IBLA and the conventional reconstruction arm) comparable, patients with a non-repairable proximal ACL rupture will be replaced by a new patient even if they were randomized to the conventional ACL reconstruction. These patients will be seen as excluded from the randomized medical device (but not excluded from the study) and will undergo a conventional ACL reconstruction (exploratory group). These patients will be treated as a sub-population and will not be included in the primary analysis.

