#### Analysis of safety endpoints

The number of patients with SAEs will be reported per treatment arm.The proportion of patients having complications will be compared between the different treatments using a Chi-square test.

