## Abbreviations

ACL: Anterior cruciate ligament
ADE: Adverse device effect
DIS: Dynamic intraligamentary stabilization
eCRF: electronic case report form
EDC: Electronic data capture
FWO: Fonds Wetenschappelijk onderzoek
HRQoL: Health-Related Quality of Life
IBLA: Internal brace ligament augmentation
ICUR: Incremental cost-utility ratio
IKDC: International knee documentation committee
MRI: Magnetic resonance imaging
QALY: Quality-Adjusted Life Year
RCT: Randomized controlled trial
SAE: Serious adverse event
VAS: Visual analogue scale

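### As worded, the complication endpoint (ADEs plus SAEs) leaves out non-serious graft-harvest morbidity, which can tilt the complication comparisons with reconstruction against repair

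*Protocol article*

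**What the plan says.** All references are to the protocol article.

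- **Secondary endpoints** gives the content of the complication endpoint: "Intra- and post-operative complications: adverse device effects (ADEs) and serious adverse events (SAEs"). No third category is named.
- **Data management and analysis software** also describes event reporting in terms of ADEs and SAEs only.
- **Analysis of safety endpoints** has two items. One is descriptive: "The number of patients with SAEs will be reported per treatment arm". The other is a test: "The proportion of patients having complications will be compared between the different treatments using a Chi-square test".
- **Secondary objectives** asks whether the repair techniques differ from reconstruction "in terms of pain and complications during and after surgery".
- **Background** says of reconstruction that "graft harvest is associated with a degree of morbidity from tissue loss". The **Discussion** lists avoiding that morbidity among the theoretical advantages of repair.
- **Abbreviations** has "ADE: Adverse device effect". The article gives no operational definition beyond this.
- **Table 1** lists complications intra-operatively and at every post-operative time point, with no device qualifier.

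**The concern.** The two components of the endpoint have different entry rules. A serious event counts whatever its cause. A non-serious event counts only through the ADE component, that is, only if a device is responsible. Taking a hamstrings tendon is a surgical step and not a device, so a non-serious donor-site problem meets neither rule. Such problems can occur only where a graft is harvested.

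The harm that drops out is therefore one the article itself attributes to reconstruction and uses as an argument for repair. A chi-square test on the resulting proportions reads as a fair comparison of complications, yet one arm has a class of event that cannot enter its count. The possible consequences are an apparent excess of complications after repair, or a real advantage of repair that the endpoint does not show.

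**Working it through.** **Step 1: which non-serious events qualify, by arm.** The techniques are as described under Study intervention.

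| Arm | Devices described | Non-serious implant problem | Graft harvest | Non-serious harvest problem |
|---|---|---|---|---|
| DIS | cord, spring-screw implant | ADE, counts | no | cannot occur |
| IBLA | tape, femoral button, bone anchor | ADE, counts | no | cannot occur |
| Reconstruction | suture button, post and interference screw | counts if ADE covers this hardware | yes | neither ADE nor SAE, not counted |

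Serious events follow one rule in all three arms. The difference lies in the last column. It touches IBLA versus reconstruction and DIS versus reconstruction, but not DIS versus IBLA.

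**Step 2: figures available.** The article gives no complication rate and no rate of harvest events. The 10% under Background is an average loss of hamstrings strength, not a proportion of patients, and cannot serve as one. The only usable figure is the arm size of 24. It reproduces: a two-sample t-test with difference 13, SD 13, two-sided alpha 0.025 and 80% power needs 20.3, so 21 per arm, and 21 / 0.90 = 23.3, so 24. The point does not depend on that calculation.

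**Step 3: patients lost from the count (assumed rates).** If a share h of reconstruction patients has a non-serious harvest event and no other counted event, 24 × h patients are missed:

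- h = 5%: 1.2 patients
- h = 15%: 3.6 patients
- h = 30%: 7.2 patients

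**Step 4: effect on the test if true totals are equal (assumed rates).** Let the true all-cause proportion be 30% in both arms, with reconstruction recorded lower because harvest-only patients drop out. The probability of a significant result with repair worse comes from summing the two binomial distributions exactly (24 per arm, two-sided 5%):

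| Repair recorded | Reconstruction recorded | Uncorrected chi-square | With continuity correction |
|---|---|---|---|
| 30% | 30% | 2.6% | 1.0% |
| 30% | 25% | 5.9% | 2.5% |
| 30% | 15% | 24.4% | 12.6% |

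The last row requires half of all reconstruction complications to be harvest-only and non-serious (15 / 30).

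**Step 5: effect if harvest adds to an otherwise equal rate (assumed rates).** Let counted events occur in 20% of both arms, and let harvest events occur independently in a share h of reconstruction patients. The true reconstruction proportion is 0.20 + 0.80 × h:

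- h = 10%: 28%, a true difference of 8 points
- h = 30%: 44%, a true difference of 24 points

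Both would be recorded as 20% against 20%, so an advantage of repair would go unseen. Here the error is a missed difference rather than a false one.

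**The case against.** **ADE is not defined here.** The article only expands the abbreviation. A full protocol may define it, or the complication form, widely enough to take in procedure-related and donor-site events. This stands as a limit: the point concerns the endpoint as worded. It does not remove the point, because the article publishes a closed pair of components, repeats the pair when describing event reporting, and attaches a test to the result.

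**Collection is the same in every arm.** Table 1 does schedule complications identically for everyone, and nothing says donor-site events go unrecorded. That settles when complications are recorded. The doubt is over which recorded events enter the test.

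**Reconstruction uses implants too.** True, and it narrows the imbalance if ADE covers them. It does not bring harvest morbidity in. A reader might infer that ADE means the repair implants only, from the Study design text on patients with non-repairable ruptures: "These patients will be seen as excluded from the randomized medical device (but not excluded from the study"). That sentence concerns the handling of those patients, including any randomized to reconstruction. It does not define ADE and should not be used to widen the claim.

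**Harvest harm is measured elsewhere.** VAS pain is collected at every post-operative visit and isokinetic strength at weeks 13, 26 and 52. So it would be wrong to infer that the trial as a whole cannot see harvest morbidity. Those measures do not, however, enter the complication comparison.

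**The earlier trial.** A reader might link this definition to the excess of related adverse events after DIS that the Background reports from a previous randomized trial. The documents do not give that trial's event definition, so the link is not supported.

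**Conclusion.** The point holds for the wording of the endpoint. Followed as written, non-serious harvest morbidity is left out of the chi-square comparison, while non-serious implant problems are counted in any arm whose devices ADE covers. The direction follows from the definition: against repair, or towards hiding an advantage of repair.

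The scope is limited. One randomized contrast (IBLA versus reconstruction) and one non-randomized contrast (DIS versus reconstruction, where the article already promises cautious conclusions) are affected, on one secondary safety endpoint. The primary outcome and the sample size are untouched.

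The size is unknown. The figure of about 24% rests on an assumed 30% true rate in both arms, half of the reconstruction complications being harvest-only and non-serious, all 24 patients per arm evaluable, and no continuity correction. With the correction it is about 13%. In the milder case (reconstruction recorded at 25%) it is 5.9% or 2.5%. A reader might conclude that the safety comparison is shown to be biased by a known amount, or that harvest events cannot count under any definition. The article supports neither, since it gives no rates and no operational definition of ADE.

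**What to change.** Define the compared complication endpoint identically in all arms: any intra- or post-operative adverse event related to the index procedure, including donor-site events, or to any implant, serious or not. Record it at the visits where Table 1 already lists complications, using the same donor-site and implant-site checklist for every patient. Apply the chi-square comparison to that endpoint and report ADEs and SAEs as subsets. If the full protocol already defines complications this way, one clarifying sentence is enough.

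The cost is a reworded endpoint and one checklist in the eCRF, with no extra visits. The downside is slightly more event entry and higher complication counts, mainly in the reconstruction arm. Nothing in patients' treatment changes.

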#### DIS

The DIS repair technique was described by Eggli et al. (Fig. 4) [12]. The tibial stump of the ACL is reduced to the femoral footprint by transosseous sutures thereby restoring the anatomical position of the ACL [15]. Additional to the technique described by Eggli et al., lasso sutures will be used to reduce the tibial stump, if the stump cannot be reduced with PDS sutures. With this adaption, multi-bundle ruptures can be repaired. The knee is stabilized with a strong polyethylene cord which is passed on the tibial side behind the tibial footprint to prevent damage to the ACL tibial blood and nerve supply. At the femoral side the cord is passed through the anatomical footprint after carrying out micro-fracturing at this site. Using a dynamic spring-screw implant, the cord is brought under tension on the anteromedial aspect of the tibia just above the pes anserinus insertion. The proximal tibia is hereby pulled in a constant posterior drawer position with a force of 50–80 Newton depending on the sex of the patient. It is hypothesized that DIS repair continually stabilizes the knee and therefore can enable mechanically stable ACL healing [12].

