MRI is performed on a 3 T system (Magnetom Prisma Tim, Siemens, Erlangen, Germany) for IBLA and ACL reconstruction arms. For patients treated by DIS, a 1.5 T system (Magnetom Aera Tim, Siemens, Erlangen, Germany) with metal artefact reduction sequences will be used. The 4-level Howell classification, originally proposed for grading ACL graft, is adapted for evaluating the repaired ligaments [44]. The morphology and signal intensity of the ACL graft or repair will be subjectively assessed on conventional MRI [45].

When re-surgery is needed or a failure occurs, the patient is not excluded from the study and the follow-up will continue according to this protocol. Under re-surgery, we consider all surgeries a patient undergoes on the side of the injured knee affecting his/her mobility. Re-surgery following re-rupture will be considered as a failure.

If the proximal ACL rupture is not suitable for repair, the patient will undergo an ACL reconstruction (exploratory group). These patients will be followed according to this protocol except for the post-operative MRI measurements on week 52 and 104, and the post-operative isokinetic measurements on week 13, 26 and 52 as these measurements are study-specific and not standard of care.

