### Sample size

The primary outcome is change in IKDC score from baseline (pre-rupture) to 6 months post-operatively. A difference in IKDC change score of 13 points between the treatment arms is considered clinically meaningful as described by Irrgang et al. and Collins et al. [46, 47]. In order to detect an effect of 13 IKDC points with 80% statistical power between any of the two treatment arms using an independent samples t-test in which alpha is 0.025 (alpha corrected for the fact that per study data set 2 tests will be performed), assuming a standard deviation of 13 on the change in IKDC score per arm (SD found in pilot study), we need 21 patients per arm. Taking into account a drop out of 10%, we need 24 patients per arm or 48 patients in total which have to be randomized.

In study 1, 24 patients per arm (DIS and IBLA) will be included and in study 2, 24 patients per arm (IBLA and ACL reconstruction) will be included. The total number of patients to be included is 96. We expect that 50% of the patients will be included in Antwerp University Hospital and 50% in University Hospital Brussels. We also expect that the total number of addressed patients will range from 96 to 106, since we expect that about 10% of the patients will not have a repairable, proximal ACL rupture. They will not be eligible (any more) after the intra-operative confirmation and these patients (exploratory group) will not contribute the number of 96 patients needed for inclusion.

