### Statistical analyses

#### Analysis of the primary outcome

To answer the research question comparing the three treatment arms the research question is split up in three separate questions:
*Is there a difference between DIS and IBLA (≤4 weeks)?*

Results from study 1 will be used in a linear regression model with IKDC at 6 months as outcome and treatment, and IKDC at baseline as predictors. This linear regression model will allow correction for possible confounders like age, gender and working category.
*Is there a difference between IBLA (5–12 weeks) and conventional ACL reconstruction?*

Results from study 2 will be used in a linear regression model with IKDC at 6 months as outcome and treatment, and IKDC at baseline as predictors. This linear regression model will allow correction for possible confounders like age, gender and working category.
*Is there a difference between DIS and conventional ACL reconstruction?*

Results from study 1 and study 2 will be compared using a linear regression model with IKDC at 6 months as outcome and treatment, and IKDC at baseline as predictors. As this is a non-randomized comparison this model will correct for possible confounders like age, gender and working category.

For the primary analysis all patients that didn’t have a repairable, proximal ACL rupture will be excluded from the analysis (exploratory group). Patients with a failure or re-surgery will be included in the primary analysis.

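### Failure is defined only by post-operative events and the repairability verdict is not fixed before repair starts, so a repair abandoned in theatre in an eligible knee is not in itself a failure

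*Protocol article*

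**What the plan says.** All references are to the protocol article.

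- **Success and failure (Secondary endpoints).** "Success of the operation techniques defined as the number of non-failures". Failure has two limbs. One is "A re-rupture of the graft or the repaired ACL", confirmed clinically and on MRI. The other is instability: "AP translation difference of more than 3 mm (Lachman test) between the injured knee and the contralateral knee, and subjective instability complaints". Study procedures adds: "Re-surgery following re-rupture will be considered as a failure".
- **Conversion in theatre (Study design, text after Figure 1).** "If the proximal ACL rupture is not suitable for repair, ACL reconstruction will be performed". Such patients are replaced in every arm, including the reconstruction arm. They form the exploratory group and stay in follow-up.
- **Exclusion (Analysis of the primary outcome).** The section removes patients lacking a "repairable, proximal ACL rupture will be excluded from the analysis (exploratory group").
- **Criterion (Inclusion criteria).** Repairability means at least 75% contact of the distal remnant, confirmed during the operation.
- **Timing and blinding (Randomization and blinding).** Patients are randomised before proximal location and repairability are confirmed. The treating physicians are not blinded.
- **Technique (DIS).** Reduction can take two steps: "lasso sutures will be used to reduce the tibial stump, if the stump cannot be reduced with PDS sutures".
- **Expected numbers (Sample size).** "we expect that about 10% of the patients will not have a repairable, proximal ACL rupture", so 96 to 106 patients are to be approached.

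**The concern.** Re-rupture/failure is listed among the main secondary outcomes in the Abstract and is a secondary objective. A surgical technique can fail in two ways: it may not hold, or it may not be completed. The definition covers only the first.

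The boundary between an ineligible rupture and an uncompleted repair is drawn by a surgeon who knows the allocation, and the text does not say that it must be drawn before the repair is attempted. In the reconstruction arm no repair is tried, so the verdict there can rest only on inspection. In the DIS and IBLA arms it could also rest on how the attempt went. Replacing non-repairable patients in all arms keeps the arms comparable only if the verdict is reached in the same way in all of them. At stake are the success endpoint and, through the exclusion, the make-up of the primary analysis population.

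**Working it through.** **1. Where an abandoned repair goes.** Take a knee that meets the 75% criterion, in which a repair is started, given up and converted to reconstruction.

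| Route | Basis in the article | Primary analysis | Success endpoint |
|---|---|---|---|
| Labelled non-repairable | Study design; Analysis of the primary outcome | Excluded and replaced | Not stated |
| Kept in the randomised arm | Intention-to-treat (Abstract) | Included | Non-failure unless the graft re-ruptures or the knee becomes unstable |

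On neither route is the conversion itself a failure. The first route has no counterpart in the reconstruction arm. It also drops the scheduled MRI at weeks 52 and 104 (Study procedures), although a re-rupture needs MRI confirmation.

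**2. The plan's own figures.** No sample size is given for the failure endpoint. The stated size for the primary endpoint reproduces: a two-sample t-test with difference 13, SD 13 and two-sided alpha 0.025 has power 0.793 at 20 per arm and 0.815 at 21, and 21/0.9 = 23.3, rounded up to 24. Nothing here depends on the failure definition.

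**3. Expected failures per repair arm.** The Background cites stable healing in 96% for DIS and re-rupture in 2 of 42 (4.8%) for IBLA. Treating the remaining 4% for DIS as failures:

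- DIS: 24 × 0.04 = 0.96
- IBLA: 24 × 0.048 = 1.15

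So about one failure per arm of 24, or 1/24 = 4.2%.

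**4. Ceiling on conversions.** 106 − 96 = 10 patients over four arms is 2.5 per arm; equivalently 24/0.9 × 0.10 = 2.7. These are all ruptures expected not to be proximal and repairable. The share that would be abandoned repairs in eligible knees is not given and may be zero.

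**5. Effect of k abandoned repairs in one arm, added to 24 analysed patients with one failure.**

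| k | Left out | Counted as non-failure | Counted as failure |
|---|---|---|---|
| 0 | 1/24 = 4.2% | 4.2% | 4.2% |
| 1 | 4.2% | 1/25 = 4.0% | 2/25 = 8.0% |
| 2 | 4.2% | 1/26 = 3.8% | 3/26 = 11.5% |
| 3 | 4.2% | 1/27 = 3.7% | 4/27 = 14.8% |

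The first such patient moves the rate by 8.0 − 4.2 = 3.8 points. If the patient is not replaced and the denominator stays at 24, the move is 2/24 − 1/24 = 4.2 points. The row k = 3 is an upper bound that treats every expected conversion as an abandoned repair.

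**The case against.** The strongest reply is that the article never describes a repair that is begun and given up. Every conversion it mentions concerns a rupture that fails an inclusion criterion with a numerical threshold, applied in all arms. Since the reconstruction arm can be judged only by inspection, the natural reading is an eligibility check. The lasso-suture step widens what can be repaired, and nothing links a failed lasso to the exploratory group. Intra-operative complications are recorded and compared between treatments. Re-rupture or instability is a coherent definition of failure, and coding of rare theatre events may sit in the full protocol.

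Much of this stands, and it rules out several stronger readings that a reader might infer:

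- *That an abandoned repair can never be a failure.* A converted patient can still fail later, because the definition names the graft.
- *That such patients drop out of the success endpoint.* Exclusion is stated only for the primary analysis.
- *That the reported failure rate would be about half the true one.* That needs an assumed share of abandoned repairs, for which the article gives no basis.
- *That study 1 would favour the repair that is harder to complete.* The article gives no completion rates for DIS or IBLA.

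The reply does not remove the gap. The criterion is said to be confirmed during the operation, not before a repair step. The complications endpoint is specified as adverse device effects and serious adverse events. A remnant that cannot be reduced need be neither, and complications do not enter the success count. The two-step reduction at least shows that a first attempt may not succeed.

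**Conclusion.** The point holds in a limited form. Failure has only post-operative components, and the verdict that removes a patient from the primary analysis is made after randomisation, unblinded, and without being tied to a moment before repair. A repair abandoned in an eligible knee is therefore not in itself a failure, and one of its two possible routes exists only in the repair arms. Against reconstruction, either route can only flatter the repair arm's success rate; between DIS and IBLA no direction can be claimed.

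The size is about 4 percentage points of an arm's failure rate per such patient, assuming about one expected failure per arm of 24. The number of such patients is unknown and could be none. Even at the upper bound, 4 of 27 against an assumed 1 of 24 in a comparator gives a Fisher exact p of 0.35, so what is affected is mainly the descriptive success rate. No stated figure is wrong and the sample size is untouched. This is an inexpensive improvement that closes a route to bias.

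**What to change.** 1. In every arm, record the verdict on the 75% contact criterion at arthroscopy, time-stamped, before any repair step.
2. Limit the exploratory group, and the replacement and exclusion that go with it, to ruptures that fail the eligibility criteria at that inspection.
3. Keep a patient converted after a positive verdict in the randomised arm for the primary analysis.
4. Count that conversion as a technique failure in the success endpoint, and show the result under the current re-rupture/instability definition beside it. State which definition governs the analysis set without failures.

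This classifies an event and leaves every surgical decision as it is. The cost is one eCRF item and a sentence in the failure definition, and possibly a slightly less favourable success rate for repair.
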